## Abstract

**Background:**

The Federal Maternal, Infant, and Early Childhood Home Visiting (HV) Program serves over 100,000 vulnerable families at risk for child abuse in the USA and aims to improve many outcomes, including maternal mental health (HRSA’s Federal Home Visiting Program: partnering with parents to help children succeed, 2017). Most clients are insured by Medicaid, and about 40% are adolescent mothers (pregnant and post-delivery) (The mother and infant home visiting program evaluation: early findings on the Maternal, Infant, and Early Childhood Home Visiting Program, 2015). Over a third of home-visited clients report peripartum depressive symptoms (The mother and infant home visiting program evaluation: early findings on the Maternal, Infant, and Early Childhood Home Visiting Program, 2015). Family conflict increases rates of peripartum depression in adolescent mothers (J Ped Health Care 21:289–98, 2007; J Emot Behav Disord 5:173–83, 1997; Fam Relat 47:395–402, 1998; Arch Ped Adolesc Med 150:64–9, 1996; Obstet Gynecol 110:134–40, 2007; Am Fam Physician 93:852–58, 2016). Although home visitors screen for depression and refer those with positive screens for treatment (The mother and infant home visiting program evaluation: early findings on the Maternal, Infant, and Early Childhood Home Visiting Program, 2015), home-visited mothers infrequently obtain treatment or do not complete it if they do obtain it (Curr Probl Ped Adolesc Health Care 46:124–9, 2016; Making a difference in the lives of children and families: the impacts of Early Head Start Programs on infants and toddlers and their families, 2002; Depression and low-income women: challenges for TANF and welfare-to-work policies and programs, 2001; Aggress Violent Behav 15:191–200, 2010) due to many barriers (e.g., lack of child care, lack of transportation, geographical distance) (Arch Gen Psychiatry 68:627–36, 2011). There is a need for a video-based, family-oriented treatment for peripartum depression that is integrated into home visiting and would bypass these barriers. This article outlines a protocol for a pilot study that will explore the feasibility and acceptability of implementing a family-based treatment, using HIPAA-compliant video-based communication technology, for adolescents with peripartum depressive symptoms within the context of home visiting.

**Methods:**

This study protocol includes a description of an implementation-effectiveness hybrid trial design that will include 12 depressed adolescent mothers and their family members and a historical comparison group of 12 previously enrolled adolescent mothers.

**Discussion:**

The study results will provide a clearer understanding of whether or not video-based, family-oriented treatment is feasible and acceptable to implement within the context of home visiting and with home-visited adolescents with peripartum depressive symptoms. The findings from this pilot study could serve as a catalyst for future research that influences mental health practices and policies.

**Trial registration:**

NCT03282448, ClinicalTrials.gov date of registration 09/21/2017.

## Background

The Federal Maternal, Infant, and Early Childhood Home Visiting (HV) Program serves about 160,000 vulnerable families at risk for child abuse throughout the USA and aims to improve several outcomes, including maternal mental health [1]. About 40% are adolescent mothers (pregnant *and* post-delivery), and over a third of adolescent and adult mothers report clinically significant peripartum depressive symptoms [2]. Untreated maternal depression can lead to dysfunctional parent-child interaction [3] and an increased risk for child maltreatment [4]. Furthermore, research has shown that relational factors, such as discomfort with trust, result in poor home visiting impacts for children of depressed mothers. For example, research has shown that home visiting did not improve cognitive development or reduce behavioral problems in children of home-visited mothers with both severe depressive symptoms and discomfort with trust [5].

The addition of depression screening and mental health service referral to HV programs does not equate to receipt of treatment for all mothers. HV programs establish agreements with community mental health centers and providers to facilitate the coordination of services for depressed mothers [6]. Home visitors are expected to screen and identify depressed mothers and to make referrals for treatment. Yet, those who are referred for treatment infrequently obtain it or do not complete it if they do obtain it [6–9]. Commonly reported barriers to mental health treatment include logistical factors (e.g., no child care, lack of transportation, geographical distance) [10] and stigma for some families [11, 12]. Thus, home-visited depressed mothers have limited access to evidence-based treatment [6].

An evolving body of research on home visiting enhancements includes the addition of treatment to address unmet maternal mental health needs [13]. Enhancing HV programs with in-home delivered mental health services may be effective but not feasible in rural communities. For instance, two individual-level cognitive-behavioral therapies and one interpersonal psychotherapy model for maternal depression have been studied [14–16]. These interventions are delivered by clinicians in homes [14–16]. The sustainability of these interventions in some communities is questionable, in large part because of the financial cost of paying clinicians to travel to family homes. Mental health clinicians have significant barriers (e.g., geographical distance, financial and time constraints) that prevent them from making round-trip visits to family homes. Feasibility problems for in-home delivered mental health treatment are compounded in rural communities due to the mental health workforce shortage and even greater clinician travel time that can triple the cost of therapy. For these reasons, technology offers a feasible strategy to provide treatment in the home.

Furthermore, family conflict is a risk factor for peripartum depression and a consequence of it [17–20] and individual-level treatments do not typically address family dynamics. Low family cohesion, high criticism, and low parental connectedness are related to worsening of depressive symptoms and treatment outcomes in adolescent mothers [18–25]. These findings support a need for a family-based treatment for adolescent mothers with peripartum depressive symptoms. Although individual therapy and psychiatric medication management that is delivered using HIPAA-compliant video-based communication technology is covered by many health insurance companies, video-based family therapy using this same technology is not currently a covered service. Although a few controlled studies conducted in other countries have shown that web-based family psychoeducational interventions are effective in preventing postpartum depression (e.g., [26–28]), to our knowledge this is the first study of a video-based family therapy intervention for adolescent mothers with peripartum depressive symptoms.

### Study purpose and aims

The purpose of the current study is to partner with two Federal HV Program sites to implement a family-based intervention, using HIPAA-compliant video-based communication technology, for use with home-visited adolescents with peripartum depressive symptoms and their families living in rural communities. The study intervention is informed by Rathus and Miller (2014), *Dialectical Behavior Therapy (DBT) Skills Training for Adolescents*, which includes a multifamily group format [29]. The DBT skills used in the study intervention target three types of regulation (cognitive, emotion, and behavior) that influence and are influenced by relational dynamics [29–32]. A variety of DBT principles and skills have been applied to couples and families to reduce conflict, increase validation, and improve emotion regulation and problem-solving [30, 31]. Research has shown that the DBT model [29], which includes individual therapy with intersession skills coaching and multifamily skills groups, is effective in reducing suicide attempts [33], self-injury [34], interpersonal conflict [32, 35, 36], and depressive symptoms [32, 36] in adolescent populations with more severe psychopathology than in those who will be recruited for the current study. To our knowledge, this is the first study to explore the feasibility and acceptability of implementing a video-based, DBT-informed intervention with adolescent mothers with peripartum depressive symptoms.

The study has three aims. First, the feasibility and acceptability of integrating the treatment model into two Federal HV Program sites in New England will be explored. Evidence of feasibility will be demonstrated by the home visitor identification of eligible families for recruitment, adherence to education of families in the use of HIPAA-compliant video-based communication technology, and adherence to coping skill reinforcement statements in home visits. Evidence of acceptability will be demonstrated by high HV staff responsiveness through attendance at all trainings and implementation meetings, home visitor attendance at all supervision sessions with the therapist, and home visitor report of high satisfaction, usefulness, and relevance of treatment involvement.

Second, we will explore the feasibility and acceptability of the treatment model among depressed adolescent mothers and their families. Evidence of feasibility with this population will be demonstrated by quality of delivery (strong therapist-family working alliance) and retention of at least 80% of families. Evidence of acceptability with this population will be demonstrated by high family responsiveness through completion of homework assignments and report of high satisfaction with treatment.

Finally, we will explore preliminary impacts of the treatment on maternal depressive symptoms and parental empathy, and family emotion regulation and family functioning at 2 months post-intervention. We hypothesize that mothers will show a clinically meaningful reduction in depressive symptoms and improvements in parental empathy at 2 months post-intervention. When compared to adolescent mothers who were previously enrolled in home visiting, those who received the study treatment will show preliminary evidence of a greater reduction in depression. We also hypothesize that families will show clinically meaningful improvement in emotion regulation and family functioning.

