### Community-based collaboration

Our study is consistent with the community engagement research framework whereby researchers engage communities in study and intervention development and implementation planning (e.g., [37]). Most community engaged research on mental health treatment has been conducted in urban settings without attention to the translational aspects of such interventions to rural communities (e.g., [38–40]). The current community-based research study was developed through a collaborative process involving researchers, Federal HV Program site leaders, and State-level Maternal and Child Health administrative leaders. We identified an efficient way to integrate home visitor training into standard HV program operations since the study’s training aligns with a national HV benchmark [1] that pertains to maternal depression. We developed a study implementation plan and ensured that home visitor study responsibilities would not interfere with their job responsibilities.

Furthermore, we conducted a preliminary small research study that produced findings that suggested a need to integrate the video-based, family-oriented treatment into the two Federal HV Program sites. Its purpose was to explore home visitor interest in supporting adolescent mothers’ mental health treatment and to explore family attitudes towards video-based family mental health treatment. Home visitors, mothers, and family members were recruited from September 2016 through December 2016. Home visitors, mothers, and their family members anonymously completed web-based surveys on a secure, password-protected website. Five home visitors, six adolescents, and three of their family members completed the surveys. For the home visitor survey, we adapted items from a reliable and valid needs assessment [41] and added items on family support team responsibilities. For the maternal and family member surveys, we adapted items from reliable and valid treatment motivation [42] and stigma [43] scales and added items on video-based family therapy.

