### Participant selection

The two Federal HV Program sites employ a total of 10 home visitors and serve about 44 families in three counties in New England. Eight home visitors and 12 adolescent mothers (pregnant *and* post-delivery), ages 13–25 years old, and their family members (six families per site) will be recruited. “Family member” is defined as one who is biologically related to the adolescent mother or a significant close other with whom she is not biologically related. The sample size was determined in consultation with our external community stakeholders. They recommended that we implement the protocol in two different Federal HV Program sites with a small number of families (i.e., 6 per site) in order to obtain early evidence of feasibility (e.g., implementation strategies such as staff training, research strategies such as family recruitment and retention) and acceptability (e.g., perceived agency burden, family receptivity) in preparation for larger studies of potential effectiveness and scalability.

This study also includes a historical comparison comprised of 12 depressed adolescent mothers who were previously enrolled in home visiting and have similar characteristics to those who will be recruited for the study. We will match the previously enrolled adolescent mothers to intervention group mothers based on scores of the *Edinburgh Postnatal Depression Scale* (*EPDS*) [45] administered at equivalent time intervals, maternal age, home zip code, pregnancy trimester or infant age for postpartum adolescents, relationship status, average annual income, and highest level of education.

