#### Study measures

Treatment implementation practices and both process and outcome measures will guide the translation of research to clinical practice. Process measures include indicators of feasibility (knowledge, adherence, quality of delivery, and retention) and acceptability (home visiting staff and family responsiveness). The process measures were selected using criteria by Mowbray, Holter, Teague, and Bybee (2003) [46]. The study measures are presented in Table 1.

**Table 1 Tab1:** Study measures by aim, construct, respondent, and time point

Construct	Measure	Respondent			Time point		
		Mother	Family	Home visitor	O_1_	O_2_	O_3_
1. Feasibility and acceptability of implementing the treatment in HV.							
Knowledge	Pass test on the use of video software.			X	X		
	Percent of eligible families identified.^a^			X		X	
Adherence	Percent of families educated in use of video software.^b^			X		X	
	Percent of visits with coping skill reinforcement.^b^			X		X	
Home visiting Staff responsiveness	Percent of training sessions attended.^a^			X	X		
	Percent of supervision sessions attended.			X		X	
	Percent of implementation meetings attended.^a^			X		X	
	Satisfaction, usefulness, and relevance of family support team responsibilities from focus groups.			X			X
2. Feasibility and acceptability of implementing treatment with families.							
Quality of delivery	Working Alliance Inventories—therapist and client versions [49, 50].^c^	X	X			X	X
Retention	Percent of families who complete treatment.	X	X				X
Family responsiveness	Percent of completed homework assignments.	X	X			X	
	Satisfaction questionnaire developed by team.	X	X				X
3. Evidence of clinical effectiveness of the treatment.							
Depression	SCID-V Depression Module [55]; NIMH DISC-Y and DISC-P Mood Module for those under 18 [56].^d^	X				X	
	Beck Depression Inventory-II (BDI-II) [57].^d^	X				X	X
Emotion regulation	Emotion Regulation Questionnaire (ERQ) [58], ERQ Child and Adolescent Version for those under 18 [59].	X	X			X	X
Parental empathy	Adult Adolescent Parenting Inventory-II (AAPI-II) [60].	X				X	X
Family functioning	Protective Factors Survey, Family Functioning/Resiliency subscale [61].	X	X			X	X

^a^Co-investigators will monitor recruitment of families and record HV staff attendance

^b^Based on home visitor report to the therapist

^c^Monitoring measure, also completed by therapist, at the end of therapy session 6

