### Planned analyses

The planned analyses are organized by study aim. For the first aim, univariate statistics will be used to characterize indicators of feasibility (knowledge and adherence). For knowledge of HIPAA-compliant video-based communication technology, home visitors will demonstrate their understanding of setting up and using the software on a computer and cell phone. The average number of times it takes home visitors to correctly complete this task will be calculated. Feasibility will be demonstrated by all home visitors successfully accessing the software by the second attempt. For knowledge of family eligibility, a percentage will be obtained for home visitor accuracy in identifying eligible families for participation by dividing the number of eligible families listed in the site’s database that are regularly receiving home visits. Feasibility will be demonstrated by home visitors correctly identifying at least 80% of eligible families for study participation. For adherence, the percentage of families who are educated in use of HIPAA-compliant video-based communication technology will be calculated and the ratios for actual to expected coping skill reinforcement will be calculated for each home visit and summarized overall. Feasibility will be demonstrated by home visitors educating all participating families in how to use the HIPAA-compliant video-based communication software and home visitor reinforcement of at least 80% of coping skills in home visits. For acceptability (HV staff responsiveness), univariate statistics and qualitative data analytic methods [47] will be used. For HV staff responsiveness, attendance rates will be calculated for the training, implementation meetings, and supervision sessions. Acceptability will be demonstrated by HV staff attendance at all required training activities. Home visitors will participate in focus groups held at each of the two Federal HV Program sites (see Table 1). Three experienced independent coders will code focus group transcriptions. A thematic analytic approach [48] will be used due to the semi-structured, open-ended focus group questions. The independent coders will use traditional open coding to code participants’ responses to the questions. Thematic analysis will be conducted using inductive coding [48]. The independent coders will schedule consensus meetings to discuss codes and resolve discrepancies. They will group the codes into categories to create themes, which will be identified through consensus. This iterative process will allow the independent coders to formalize the themes. The emergent themes will be identified and summarized [47].

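### The stated rule for staff acceptability (Aim 1) rests on attendance alone and omits the home visitor report that the aims require, and that report is collected with no level for high

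*Protocol article*

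**What the plan says.** In the Protocol article, Study purpose and aims gives Aim 1 acceptability two parts. The first is attendance: "high HV staff responsiveness through attendance at all trainings and implementation meetings, home visitor attendance at all supervision sessions with the therapist". The second, joined to it by *and*, is opinion: "home visitor report of high satisfaction, usefulness, and relevance of treatment involvement".

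Table 1 (Study measures) lists three attendance percentages under home visiting staff responsiveness, and one row for opinion, at O3: "Satisfaction, usefulness, and relevance of family support team responsibilities from focus groups". It lists no questionnaire or rating scale on these constructs for home visitors.

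Planned analyses (first aim) describes how the opinion data are gathered, "Home visitors will participate in focus groups held at each of the two Federal HV Program sites", and how they are handled: "Thematic analysis will be conducted using inductive coding", with three coders agreeing on themes that are then summarized. Attendance rates are calculated for training, implementation meetings and supervision. The pass rule for this construct is: "Acceptability will be demonstrated by HV staff attendance at all required training activities".

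Participant selection, in explaining the sample size, gives examples of the evidence the study should yield, among them "acceptability (e.g., perceived agency burden, family receptivity".

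**The concern.** The aims set a level (*high*) for staff opinion, but the method chosen yields themes, which have no level. The section that fixes the pass marks then leaves opinion out. A reader of the results could be told that home visitors found the added role acceptable on the strength of attendance, when their own report was lukewarm or negative.

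Acceptability to staff is one of the main things this pilot is meant to establish before larger studies. A rule that cannot respond to what staff report gives weak support for that step.

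**Working it through.** There is no figure in the plan to reproduce. The check traces each part of the criterion from the aims to the analysis.

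| Component of Aim 1 acceptability | In the aims | In Table 1 | Quantity in Planned analyses | Pass rule in Planned analyses |
|---|---|---|---|---|
| Training attendance | Yes, all | Yes | Rate | Yes, all required activities |
| Implementation meetings | Yes, all | Yes | Rate | Only if counted as required training activities |
| Supervision attendance | Yes, all | Yes | Rate | Only if counted as required training activities |
| Satisfaction, usefulness, relevance | Yes, high | Focus groups only | None (themes) | None |
| Perceived agency burden | Not in the aims; an example in Participant selection | No row | None listed | None |

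**Step 1: what the two sections would conclude.** Take the wider reading, in which the required training activities cover all three kinds of session.

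- Attendance full, report favourable: the aims are met and the rule is met.
- Attendance full, report unfavourable: the aims are not met, but the rule is met.
- Attendance not full: neither is met, whatever the report.

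The sections disagree in exactly one case, which is the one where staff opinion matters. On the narrow reading (training only) they also disagree when training is complete but supervision or implementation meetings are missed. On both readings opinion plays no part in the rule.

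**Step 2: whether *high* can be judged at all.** The analysis gives no score per visitor, no count of favourable views and no definition of a favourable theme. So even a team that wished to apply the aims in full has no stated way to say whether the second part is met.

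**Step 3: whether this is just detail left to a fuller document.** Planned analyses gives explicit marks for the other Aim 1 indicators: software access by the second attempt, at least 80% of eligible families identified, all participating families educated, and at least 80% of coping skills reinforced. For Aim 2 it gives alliance means of 5 or above, 70% of sessions attended, and one homework assignment per module. The article therefore chose to state its rules in this section, and the one stated for staff acceptability omits a component that the aims require. That is a conflict within the text.

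**Step 4: what a count would look like.** With eight home visitors, 6/8 = 75% and 7/8 = 87.5%. The 80% mark used elsewhere in Aim 1 gives 0.80 × 8 = 6.4, so in practice it means 7 of 8. A cut-off is better written as a count than as a percentage.

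**The case against.** The strongest reply is that the criterion in the aims is conjunctive, so declaring acceptability against negative themes would breach the aims. The Discussion also commits to comparing qualitative and quantitative data for consistency to inform changes to the protocol and design. Focus groups are a legitimate way to explore acceptability with eight staff in a pilot. All of this stands, and it means the themes will be used. It does not supply a level for *high*, and it does not change the rule in Planned analyses.

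Several stronger readings are tempting, and the documents do not support them:

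- *Burden is not measured.* The focus-group questions are semi-structured and the guide is not shown, so burden may be asked about there. What can be said is that no burden measure or analysis is listed. Burden is also an example in the sample-size rationale, not a criterion in the aims.
- *Only training attendance counts.* Rates are calculated for implementation meetings and supervision too, and the rule may be meant to cover them.
- *Attendance is merely job duty.* Community-based collaboration says the team found a way to "integrate home visitor training into standard HV program operations"; it does not say this of supervision or implementation meetings. Home visitors join willingly and give consent. Sustained attendance is some evidence of acceptability, though not a substitute for the report.
- *Dissent will be lost in a consensus theme, in groups of about four colleagues.* The consensus is among the coders, not the participants. Nothing says minority views are dropped. Moderation and confidentiality are not described, and four per group assumes an even split between sites that is not stated.

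The family satisfaction measure is also a limited comparator. It has multiple-choice items that are averaged, but no cut-off. It shows that rated items fit this study, not that a working rule exists for families.

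**Conclusion.** The point holds as a mismatch between the aims and the planned analysis. Aim 1 acceptability has an attendance part and an opinion part. The opinion part has no level and no rule, and the only pass rule stated can be satisfied whatever staff report. The missing burden measure is a secondary gap, subject to what the unseen focus-group guide contains.

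No numerical error or bias is claimed, and the finding does not depend on power, group size or how candid the focus groups turn out to be. It rests on reading the rule in Planned analyses as the operative one for this construct, which is how that section treats its other indicators. It should be corrected, because the remedy is cheap and the conclusion affected is one of the pilot's main ones.

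**What to change.** 1. In Table 1, add at O3 a short, individual, confidential rating form for each home visitor, covering satisfaction, usefulness, relevance and burden.
2. In Planned analyses, restate the rule so that Aim 1 acceptability requires both the attendance criterion as given in the aims (trainings, implementation meetings and supervision) and a pre-set rating level stated as a count, for example 7 of 8 visitors favourable. Say what the count becomes if fewer than eight respond.
3. Keep the focus groups and their thematic analysis to explain the ratings.

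At minimum, without a new form, reconcile Planned analyses with the aims so that attendance alone cannot demonstrate acceptability. One way is to present the staff report as a descriptive qualitative result and to report attendance without calling it a demonstration of acceptability.

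The cost is one brief form for eight people and a few sentences of text. The downsides are a few minutes of respondent time, limited anonymity among eight staff at two sites, and a cut-off that could be missed. With eight respondents the count is a coarse guide and should be reported as such.
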